| Tumor tissue sample**^17^** | **X** | |  |  | **X** |  |  |
| **Notes:**   1. The screening period has a window of 28 days, the treatment period has a window of ±3 days (with a tumor assessment window of ±7 days), the end-of-treatment visit has a window of ±7 days, and the follow-up period has a window of ±7 days. During the screening period, ECOG performance status, hematology, blood biochemistry, coagulation, urinalysis, T3 or FT3, FT4, and TSH must be recorded within 7 days prior to the first dose and meet the corresponding inclusion and exclusion criteria for enrollment. 2. All prior treatments within 30 days before signing the ICF and all concomitant treatments from the signing of the ICF until the discontinuation of study treatment will be documented; thereafter, concomitant treatments for SAEs related to the study drug need to be documented. 3. Height examination is only performed in the screening period; vital signs include body temperature, pulse, respiratory rate and blood pressure. Body weight will be measured prior to each dose. If the subject's weight during the study changes by ≤10% compared to the baseline reference weight, no dose adjustment of the study drug is required. If the weight change exceeds 10%, the dose needs to be recalculated. 4. AEs and SAEs should be recorded from the signing of the ICF until 30 days after the last dose of the study drug. 5. Gastroscopy and pathology tests: Subjects must complete gastroscopy and pathology tests during the screening period after meeting the enrollment criteria and signing the informed consent form to determine the distance between the tumor and the incisors and collect tumor tissue specimens for subsequent laboratory tests. If gastroscopy and pathology tests have been performed at an external institution, gastroscopy must be repeated at this study site, but there are no requirements for pathology tests. 6. PD-L1 expression of gastric cancer: Subjects must complete the immunohistochemical PD-L1 expression and CPS scoring of gastric cancer tissues during the screening period after meeting the inclusion criteria and signing the informed consent form. They need to be completed at this study site. 7. MSI status of gastric cancer: Subjects must complete the immunohistochemical MSI status testing of gastric cancer tissues during the screening period after meeting the inclusion criteria and signing the informed consent form. They need to be completed at this study site. 8. Serplulimab will be administered on Day 1 of each 3-week treatment cycle after completion of all clinical and laboratory procedures/assessments. During the neoadjuvant phase, treatment consists of 3 cycles with a dose volume of 300 mg/dose. The dosing window is within ±3 days of the scheduled time point. 9. After completion of all clinical and laboratory procedures/evaluations, neoadjuvant therapy will be administered using the standard SOX regimen (oxaliplatin + Tegafur), with 3 weeks as one treatment cycle, and neoadjuvant therapy consists of a total of 3 cycles. Oxaliplatin will be administered on Day 1 of each cycle at a dose of 130 mg/m^2^, via intravenous infusion over 2–6 hours (chemotherapy drugs will be administered after the completion of Serplulimab infusion). If the body surface area exceeds 2.0 m^2^, the dose is calculated based on 2.0 m^2^. Tegafur will be administered orally according to the body surface area as below: <1.25 m^2^, 40 mg/dose; ≥1.25 to <1.5 m^2^, 50 mg/dose; ≥1.5 m^2^, 60 mg/dose; twice daily, from Day 1 to Day 14 of each treatment cycle. 10. After completion of all clinical and laboratory procedures/assessments, thymalfasin 4.8 mg will be administered via subcutaneous injection, twice weekly starting from Day 1 of neoadjuvant therapy. On Day 1 and Day 4 of each week during Weeks 1–9. 11. Routine laboratory tests include hematology, blood biochemistry, urinalysis, and coagulation function. The hematology items include complete blood count with differential. The blood biochemistry items include blood urea/urea nitrogen, creatinine, sodium, potassium, magnesium, chloride, bicarbonate/carbon dioxide combining power/total carbon dioxide (TCO2), calcium, phosphorus, glucose, total bilirubin, direct bilirubin, alanine aminotransferase (ALT), aspartate aminotransferase (AST), alkaline phosphatase, lactate dehydrogenase, total cholesterol, total protein, and albumin. The urinalysis items include specific gravity, pH, glucose, protein, casts, ketones, and blood cells. Coagulation function tests include activated partial thromboplastin time (APTT), prothrombin time (PT), and international normalized ratio (INR). The tests should be performed within 7 days before the first dose, within 3 days before dosing in Cycle 3, within 7 days before surgery, and within 3–7 days after surgery. If the laboratory tests and study drug administration are scheduled on the same day, the study drug cannot be administered until the test results are obtained. The analysis will be conducted in this study site. 12. Thyroid function tests include analysis of triiodothyronine (T3 or FT3), thyroxine (T4 or FT4), and thyroid-stimulating hormone (TSH). The tests should be performed 7 days before the first dose, 3 days before dosing in Cycle 3, 7 days before surgery, and within 3–7 days after surgery. The analysis will be conducted in this study site. 13. Cardiac function markers include: myocardial enzymes [creatine kinase (CK) and its isoenzymes], troponin (TnT or TnI), and brain natriuretic peptide (BNP and/or NT-proBNP). The tests should be performed 7 days before the first dose, 3 days before dosing in Cycle 3, 7 days before surgery, and within 3–7 days after surgery. The analysis will be conducted in this study site. 14. Tumor markers must include: carcinoembryonic antigen (CEA), carbohydrate antigen CA19-9, and alpha-fetoprotein (AFP). The tests should be performed 7 days before the first dose, 3 days before dosing in Cycle 3, 7 days before surgery, and within 3–7 days after surgery. The analysis will be conducted in this study site. 15. Pre-transfusion eight-item panel: All subjects must undergo hepatitis B surface antigen (HBsAg) and hepatitis B core antibody (HBcAb) testing during the screening period. For subjects with HBsAg (+) or HBcAb (+), further hepatitis B virus (HBV) DNA titer testing is required. At screening (baseline), in case of HBV DNA (-), and either 1. HBsAg (+), or 2. HBcAb (+), HBsAg (-), then HBV surface antigen/core antibody and HBV DNA must be tested every 2 cycles during treatment, before the surgery, at treatment discontinuation, and during safety follow-up. 16. CT or MRI imaging examinations should be performed within the screening period, within 7 days before treatment in Cycle 3 of neoadjuvant therapy, within 1 week after completion of neoadjuvant therapy, and after the surgery until the initiation of adjuvant therapy (recommended 4–12 weeks after the surgery). Throughout the study period, the examination methods should remain as consistent as possible. Abdominal CT scans require dual-phase (arterial and venous) imaging, performed under fasting conditions with the intake of at least 1000 mL of water or contrast agent. Contrast agents should be used unless contraindicated. The investigator assesses tumor imaging findings according to RECIST v1.1 (the frequency of tumor assessments may be increased as clinically needed at the investigator's discretion). The investigator should determine subsequent treatment based on the efficacy evaluation results. If tumor assessment has been performed within 28 days prior to the first dose, and the same method and equipment are used at the same hospital, it may serve as the baseline tumor assessment. 17. Subjects must provide formalin-fixed, paraffin-embedded (FFPE) tumor samples (paraffin blocks or unstained sections) collected from the lesion site at or after GC diagnosis (preferably within 2 months before the first dose of the study drug), along with relevant pathological reports of the aforementioned specimens. If the subject does not have archived tumor tissue samples that meet the requirements, a fresh tumor lesion biopsy must be performed during the screening period to obtain corresponding tumor samples (the number of specimens collected will be determined based on the biopsy). Additionally, surgically excised tumor tissue specimens will be retained postoperatively. Tumor tissue section samples will be used for determination of PD-L1 expression levels and MSI testing. | | | | | | | |

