**The usage and dosage of each study drugs are as follows:**

- Serplulimab: 300 mg/dose, intravenous infusion, D1, once every 3 weeks.
- Thymalfasin: 4.8 mg, subcutaneous injection, twice a week. On Day 1 and Day 4 of each week during Weeks 1–9
- Chemotherapy: SOX regimen

Oxaliplatin: 130 mg/m^2^, intravenous infusion over 2–6 hours (administered after completion of Serplulimab infusion), D1, once every 3 weeks; if the body surface area exceeds 2.0 m^2^, the investigator may calculate the dose based on 2.0 m^2^ according to actual conditions;

Tegafur: Taken orally twice daily from Day 1 to Day 14 (D1–D14) based on body surface area, with 3 weeks (21 days) as one treatment cycle.

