**Body surface area (m^2^), first dose (as Tegafur):**

<1.25 m^2^, 40 mg/dose

≥1.25 m^2^ to <1.5 m^2^, 50 mg/dose

≥1.5 m^2^, 60 mg/dose

- 1. **Postoperative Follow-up Period**

1. The occurrence of postoperative complications should be followed up within 30 days after surgery;
2. All enrolled subjects will be continuously monitored: patients who receive surgery will be followed up every 3 months within the first year after surgery and every 6 months thereafter until 2 years, with the following recorded: physical examination, laboratory test results (including tumor marker tests), imaging findings (presence of recurrence or metastasis), adjuvant treatment regimens, and treatment duration.
3. **Use of Study Drugs**
   1. **Serplulimab**

Serplulimab from Shanghai Henlius Biotech, Inc. is used in this study, with a strength of 100 mg/vial. The main active ingredient of Serplulimab is a recombinant fully human anti-programmed death receptor-1 (PD-1) monoclonal antibody, with a concentration of 10 mg/mL. This product is a clear, colorless liquid, free from foreign matter, flocculent material or precipitate. The excipients include citric acid, sodium citrate, sodium chloride, mannitol, polysorbate 80, and water for injection.

The finished product of Serplulimab should be stored protected from light at 2–8℃, with a shelf life of 36 months. If turbidity, precipitation, or other quality issues are observed in the injection solution, the product should be immediately stored in sealed containers and Henlius should be notified immediately.

The intravenous infusion time of Serplulimab should be 30–60 minutes. Do not administer by intravenous bolus or a single rapid intravenous injection. Dilution instructions for the drug prior to administration are as follows:

- Prepare the solution and perform infusion
- Do not shake the vial.
- Allow the vial to return to room temperature (25°C or below) before use.
- After taking it out of the refrigerator, the vial may be stored at room temperature (25°C or below) for up to 24 hours prior to dilution.
- Visually inspect the solution for injection for particulate matter and discoloration prior to administration. This product is a clear to slightly opalescent, colorless to pale yellow liquid, free from foreign matter. If visible particles are observed, the vial should be discarded.

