- Transfer 2 vials of this injection (300 mg) into an intravenous infusion bag containing 9 mg/mL (0.9%) sodium chloride solution to achieve a final concentration ranging from 1.5 to 5.0 mg/mL. Gently invert the dilution to mix.
- From the perspective of microbiology, the product must be used immediately after dilution and must not be frozen. Stability studies of this product indicate that it can be stored for 24 hours when protected from light at 2–8℃. This 24-hour period includes a maximum of 6 hours at room temperature (20–25℃) under indoor lighting (the 6-hour period includes administration time). After refrigeration, the vials and/or IV bags must be allowed to return to room temperature before use.
- The infusion set used must be equipped with a sterile, pyrogen-free, low protein-binding in-line filter (pore size 0.2 μm). The infusion time should be within 30 to 60 minutes.
- Do not administer simultaneously with other medications using the same infusion line.

This product is for single use only. Any unused medication remaining in the vials must be discarded.

- 1. **Thymalfasin**

Thymalfasin (brand name: Zadaxin) from SciClone Pharmaceuticals (China) Co., Ltd., with a strength of 1.6 mg, is used in this study. The storage, preparation, and administration will be performed in accordance with the instructions provided in the product package insert.

- 1. **Oxaliplatin and Tegafur**

Storage, preparation, and administration should be performed in accordance with the approved product package insert for oxaliplatin and Tegafur.

1. **Dose Adjustments**
   1. **General Principles**

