If an adverse event occurs during the study, the investigator will first determine the potential causative drug and adjust the medication based on the most severe adverse event observed in the previous dosing cycle. Prior to administration of the study drug on Day 1 of each cycle, the results of hematology and hepatic and renal function of subjects must meet the requirements for dosing, and all other toxicities must have resolved to CTCAE Grade 0–1 or baseline levels (except for alopecia, fatigue, protocol-specified exceptions, or other conditions deemed clinically insignificant by the investigator). If subjects fail to meet the medication criteria within the planned dosing interval due to adverse events, the next administration time may be delayed. If the investigator confirms that the adverse event is solely caused by one drug, the dose of that specific drug may be adjusted exclusively. If it is unclear whether the adverse reaction is related to two or more drugs, the doses of all potentially relevant drugs may be adjusted simultaneously. If a study drug needs to be temporarily suspended or permanently discontinued due to drug-related toxicity, drug-related adverse events (AEs), or other reasons, other study drugs may be administered alone provided the corresponding medication criteria are met.

All dose adjustment interventions must be documented, including the reasons and actions taken.

- 1. **Doe Adjustment of Serplulimab**

Throughout the study, dose adjustments of Serplulimab are not permitted. The principles for temporary suspension and permanent discontinuation of Serplulimab are outlined in the table below.

Table. Dose Adjustment Scheme for Serplulimab in Case of Adverse Events

| **Immune-related adverse reactions** | **Severity** | **Treatment adjustment regimen** |
| --- | --- | --- |
| Pneumonia | Grade 2 | Treatment suspension until adverse reactions resolve to Grade 0–1. |
|  | Grade 3 or 4 or recurrent Grade 2 | Permanent discontinuation |
| Diarrhea and colitis | Grade 2 or 3 | Treatment suspension until adverse reactions resolve to Grade 0–1. |
|  | Grade 4 | Permanent discontinuation |
| Hepatitis | Grade 2, aspartate aminotransferase (AST) and alanine aminotransferase (ALT) at 3–5 times the upper limit of normal (ULN) or total bilirubin (TBL) at 1.5–3 times the ULN | Treatment suspension until adverse reactions resolve to Grade 0–1. |
|  | Grade 3 or 4, AST or ALT >5×ULN, or total bilirubin >3×ULN | Permanent discontinuation |

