  - During the treatment period, drugs with hepatotoxicity (i.e., as explicitly listed in the drug package insert with warnings for hepatotoxicity) should be avoided.

1. **Management of Study Drugs**
   1. **Storage and Management of Study Drugs**

Serplulimab should be stored refrigerated at 2–8℃, protected from light and moisture; freezing is strictly prohibited. Zadaxin should be protected from light and stored at 2–8℃. All study drugs, including Serplulimab and Zadaxin, should be transported to each study site via cold chain. The study site must designate a dedicated person responsible for the storage and dispensing of the study drugs.

The study drugs Serplulimab and Zadaxin should be stored in a refrigerator accessible only to authorized personnel. Upon receipt of the drugs, the investigator must verify that the transportation temperature is within the specified range. After confirmation, the investigator should sign for the drugs and store them at the specified temperature. If temperature deviations occur during transportation or storage at the study site, the drugs should be promptly isolated and transferred to the specified temperature conditions. The drugs should not be administered to subjects temporarily, and the incident must be reported immediately for further handling according to the instructions of Henlius and SciClone.

- 1. **Drug Recovery and Destruction**

In this study, containers for used study drug may be destroyed on-site in accordance with the applicable guidelines and standard operating procedures established by the study site and local institutions. All unused study drugs must be collected and uniformly destroyed upon study completion/termination or after the expiry date.

- 1. **Records of Study Drugs**

The designated personnel at the study site must promptly document the receipt, distribution, usage, inventory, destruction, recovery, and damage of study drugs in accordance with relevant regulations and guidelines.

1. **Efficacy Evaluation**

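### Section 7.1 gives a 100 mg vial, a count of 2 vials and a 300 mg dose for serplulimab; the three cannot all be true, and 2 vials at the stated strength hold 200 mg

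*Protocol*

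**What the plan says.** Section 7.1 describes the product as supplied "with a strength of 100 mg/vial" and "with a concentration of 10 mg/mL". It gives no fill volume. The preparation steps in the same section then read "Transfer 2 vials of this injection (300 mg) into an intravenous infusion bag", diluted with saline "to achieve a final concentration ranging from 1.5 to 5.0 mg/mL".

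The dose is the same wherever the protocol states it. Note 8 of the Study Flow Chart says "treatment consists of 3 cycles with a dose volume of 300 mg/dose", and section 6.2 says "Serplulimab: 300 mg/dose, intravenous infusion, D1, once every 3 weeks". The Synopsis and section 3 also give 300 mg. Section 8.2 adds: "Throughout the study, dose adjustments of Serplulimab are not permitted".

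For thymalfasin, oxaliplatin and tegafur, sections 7.2 and 7.3 refer preparation to the package insert. Serplulimab is the only study drug whose preparation is written out in the protocol.

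**The concern.** The vial strength, the vial count and the dose in section 7.1 do not multiply out. One figure must be wrong, and it affects the sentence that tells staff how much drug goes into the bag.

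Two preparers could follow the same text and give different doses. One who works by milligrams at 100 mg/vial draws three vials and gives 300 mg. One who follows the vial count draws two and gives 200 mg. The protocol allows no serplulimab dose other than 300 mg.

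What is at stake is the dose received and what the results describe. This is a single-arm study of 30 patients with no concurrent control, so the pathologic complete response rate and the safety findings will be read as those of the 300 mg regimen. If some doses were 200 mg and nobody noticed, that description would be wrong.

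**Working it through.** **Inputs, all from the protocol**

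- Vial strength: 100 mg (section 7.1)
- Vials per infusion: 2, labelled as 300 mg (section 7.1)
- Product concentration: 10 mg/mL (section 7.1)
- Final concentration after dilution: 1.5 to 5.0 mg/mL (section 7.1)
- Prescribed dose: 300 mg on day 1 of each of 3 cycles (Study Flow Chart note 8; section 6.2)
- Planned enrolment: 30 (Synopsis; section 3)

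**Step 1. Try to reproduce the 300 mg.** Amount = vials × strength = 2 × 100 mg = 200 mg. The stated 300 mg is not reproduced.

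**Step 2. Find what would make the sentence true.**

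- Keep the strength: 300 / 100 = 3 vials.
- Keep the count: 300 / 2 = 150 mg per vial, a strength not found in the protocol.

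**Step 3. See whether the concentration settles it.** At 10 mg/mL a 100 mg vial would hold 100 / 10 = 10 mL and a 150 mg vial 150 / 10 = 15 mL. With no fill volume stated, 10 mg/mL fits either.

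**Step 4. Size of the shortfall, if 100 mg/vial is right and the count is followed.**

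- Per dose: 300 − 200 = 100 mg; 1 − 200/300 = 33.3% low.
- Per patient, if all three doses are affected: 3 × 2 = 6 vials (600 mg) against 3 × 3 = 9 vials (900 mg).
- Planned doses covered by the instruction: 30 × 3 = 90. This is a ceiling, not an estimate of the doses affected.

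**Step 5. See whether the dilution range would expose the error.** Permitted final volume = amount / concentration limit.

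| Amount in bag | Smallest volume (at 5.0 mg/mL) | Largest volume (at 1.5 mg/mL) |
|---|---|---|
| 200 mg | 200 / 5.0 = 40 mL | 200 / 1.5 = 133.3 mL |
| 300 mg | 300 / 5.0 = 60 mL | 300 / 1.5 = 200 mL |

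Both amounts meet the range at any final volume from 60 to 133 mL. The protocol does not state a bag volume. Taking a final volume of 100 mL as an assumption, the results are 200 / 100 = 2.0 mg/mL and 300 / 100 = 3.0 mg/mL, both acceptable. Above 133 mL, 200 mg would fall below the lower limit, so the range catches the error only in larger bags.

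**The case against.** The best counter-argument is that the prescribed dose is clear. The faulty sentence itself prints 300 mg beside the vial count, and no part of the protocol prescribes 200 mg. Underdosing requires a preparer to follow the count and disregard both the milligrams in the same clause and the strength given earlier in the section. That stands, and it lowers the chance of harm. It does not make the instruction correct.

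It can also be said that the vial count is the more likely slip, since strength and concentration are stated explicitly and 300 mg is repeated throughout. Section 7.1 also describes the product's appearance in two different ways, once as colourless and clear and once allowing slight opalescence and a pale yellow tint, which hints that the preparation steps came from another source. This is plausible but not proof. If the strength line is the misprint, two vials is right and no dose is wrong, so the product should be checked before the text is changed.

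Three smaller points are fair. Section 8.2 bars deliberate dose changes and says nothing about preparation; it confirms only that 300 mg is fixed. The final concentration range is a dilution requirement, not a dose check, so its failure to catch the error is secondary. And the contradiction leaves the endpoint, the sample size and the analysis methods unchanged.

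**Conclusion.** The concern holds. Section 7.1 contradicts itself on the only written preparation instruction for a fixed-dose study drug, and it should be corrected before anyone relies on it further.

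The 33.3% shortfall is conditional on two things: that 100 mg/vial is the true strength, and that the preparer follows the vial count rather than the milligrams. If either fails, the dose is 300 mg as intended. The protocol gives no evidence that a 200 mg dose was prepared, so the number affected is unknown and may be zero. The seriousness comes from where the error sits, in a live dosing instruction, and not from any effect on the statistical design.

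**What to change.** 1. Check the labelled strength of the serplulimab supplied to the site.
2. If it is 100 mg, change the count in section 7.1 to 3 vials (300 mg). If it is not, correct the strength line and make the count agree with it. The dose statements in the Synopsis, the Study Flow Chart, section 3 and section 6.2 are consistent and need no change.
3. Notify the pharmacy of the correction.
4. If dosing has begun, review the records under section 9.3, by which site staff "must promptly document the receipt, distribution, usage, inventory, destruction, recovery, and damage of study drugs". At 100 mg/vial, 2 vials used means 200 mg and 3 means 300 mg. Record any 200 mg dose as a protocol deviation.

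The cost is a one-line amendment, a pharmacy notice and a check of existing records. The design, sample size and analysis stay as they are.
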